The primary aim of the present study therefore is to examine the effectiveness of the online intervention “The Growth Factory” using a full scale randomized controlled trial (RCT) with four measurement moments. “The Growth Factory” aims to empower youth with intellectual disabilities by stimulating the development of a growth mindset and thereby positively impacting their psychosocial development. We hypothesize that adolescents in the intervention group will show larger increases in growth mindset (primary outcome). Furthermore, we hypothesize that adolescents in the intervention group will show greater improvements in empowerment, self-esteem, treatment motivation, and therapeutic alliance as well as a larger reduction of internalizing problems, attention problems, externalizing problems, and total behavior problems compared with adolescents in the control group (secondary outcomes). Finally, we hypothesize that adolescents in the intervention group will seek challenges more and will be less negatively impacted by social exclusion compared with adolescents in the control group (secondary outcomes). In addition, the secondary aim of this study is to gain insight for whom the intervention “The Growth Factory” is effective (i.e., moderation) and how the intervention works (i.e., mediation). Intervention satisfaction, level of intellectual disability (mild intellectual disability versus borderline intellectual functioning), and baseline mindset will be tested as moderators of the effects of the online mindset intervention. We hypothesize that adolescents with higher intervention satisfaction scores, borderline intellectual functioning, and a fixed mindset at baseline will show larger increases in growth mindset compared to adolescents with mild intellectual disabilities, who report less satisfaction with the intervention, and a more growth oriented mindset at baseline. In addition, we will explore whether age and gender moderate the intervention effect. Finally, we will test the mediating role of mindset on the effect of the mindset intervention on the secondary outcomes measures.

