### Procedure

Treatment coordinators of the institute and the school psychologists will screen youth for inclusion and exclusion criteria. After that, parents or legal representatives will receive an information letter containing a digital link and response letter to sign-up if they wish their child to participate in the study (active informed consent). In addition, adolescents will be informed approximately a week before the first screening by two research assistants in their classroom or group. If potential participants are absent or if they need extra information, information will be given individually. If adolescents also agree with participation, active written informed consent will be obtained. After that, participants will be randomly allocated to either intervention group or control group. Randomization will take place at individual level using a stratified block design to ensure equality between conditions. The stratified block randomization will be based on three factors: gender, age, and IQ. Parents, mentors, and teachers will be informed by a letter about the condition their child is assigned to.

Before filling out the pre-test, all participants will complete a short questionnaire containing questions regarding their living group or class and additional therapies (i.e., physiotherapy, speech therapy, social skills training). After that, the pre-test (T0) will be assessed. After the pre-test, youth in the intervention group will participate in the intervention “The Growth Factory” with six sessions lasting 25 to 40 min. Moreover, participants will receive care as usual parallel with “The Growth Factory”. Parents will also receive a login to be able to follow the sessions at home. Youth in the control group will receive care as usual. After completion of the trial participants in the control group will be given the opportunity to participate in “The Growth Factory”.

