### Instruments/measures

Instruments will be adjusted to reduce the complexity of the questionnaires for the participants with intellectual disabilities using the Dutch guideline for the development and adjustment of diagnostic instruments for people with intellectual disabilities [55]. The answering categories of the different questionnaires will be unified into one format of answering catergories ranging from ‘completelyuntrue’ to ‘completely true’, and coloured emoticons corresponding with the answering categories will be added. Difficult words and sentences will be simplified or slightly rephrased to avoid misunderstandings due to literal interpretation. The pilot studies showed the questionnaires to be suitable for youth with intellectual disabilities [46]. Table 1 shows an overview of study outcome measures and the informants that will be involved in each assessment.

**Table 1 Tab1:** Overview of assessments

	T0	Session 1–6	T1	T2	T3
Adolescent					
Mindset (MQ)	x		x	x	x
Empowerment (EMPO Youth 2.0)	x		x	x	x
Behavior problems (BPM-Y)	x		x	x	x
Self-esteem (RSES)	x		x	x	x
Treatment motivation (MYTS)	x		x	x	x
Therapeutic alliance (TASC-r)	x		x	x	x
Challenge seeking (Puzzles)	x		x	x	x
Impact of social exclusion (Cyberball game)	x		x	x	x
Intervention satisfaction (SRS)		x			
Mentor^a^					
Mindset (MQ)	x			x	x
Empowerment (EMPO Youth 2.0)	x			x	x
Behavior problems (BPM-P)	x			x	x

^a^Mentor is defined as school mentor or social worker from the group

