#### Intervention satisfaction

Participants in the intervention group will grade their satisfaction after each session of “The Growth Factory” with a score from *1* (very low) to *10* (very high). This grading system is in line with the Dutch educational system. The mean of the grades per session will provide a mean session satisfaction grade. Furthermore, the mean of these satisfaction grade scores of the six sessions will be taken to construct an overall mean intervention satisfaction grade. In addition, intervention satisfaction will be measured with a Dutch translation and adaptation of the Session Rating Scale (SRS) [67]. Participants will complete four statements, e.g., ‘The assistant listened to me today’ (relationship), ‘What we did today is important to me’ (goals and topics), ‘I liked what we did today’ (approach and method) and ‘I hope next time we will do something similar’ (overall). The original 10-cm visual analog scale will be replaced by a 5-point Likert scale ranging from ‘completely untrue’ to ‘completely true’. The average score of the four items will be taken as an indicator of the satisfaction with each session (session SRS). Subsequently, to construct an overall intervention satisfaction score (intervention SRS) the average will be taken of the session satisfaction scores of the six sessions. The scale has demonstrated a satisfactory reliability and validity in previous research [67]. Finally, participants will be asked to answer two open questions as a qualitative measure of session satisfaction: ‘What did you like about today’s session?’ and ‘What did you not like about today’s session?’

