### Statistical analyses

Following the intention-to-treat principle, the data from all participants randomized to either the intervention or control group will be analysed. Multiple imputations will be used for missing values at post-intervention and follow-up measurements. In addition, a completers only analysis will be conducted (i.e., participants that completed five or six sessions). The results will be reported in accordance with the CONSORT Statement [49].

Possible baseline differences between the two groups in background variables (e.g., age, gender) and relevant study variables will be examined using independent-sample t-tests. In case of differences at baseline, variables will be included as covariates in all models testing the effectiveness of the intervention. Furthermore, the effectiveness of the intervention will be analysed using repeated measures ANOVA for differences within subjects (i.e., pre-test, post-test, follow-up 1, and follow-up 2 measurements) and between subjects (intervention versus control group). In addition, intervention satisfaction, level of intellectual disability, age, baseline mindset, and gender will be tested as moderators of the effects of the online mindset intervention.

These moderator effects will be tested using three-way interactions in our repeated measures design. The effect of the mindset intervention on the secondary outcomes measures, (i.e., empowerment, internalizing problems, attention problems, externalizing problems, and total behavior problems, self-esteem, treatment motivation, therapeutic alliance, challenge seeking, and impact of social exclusion) might be mediated by mindset. This will be tested in several mediation analyses in Mplus [68].

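### Intervention satisfaction cannot be tested as a moderator by a three-way interaction, because only the intervention group has a satisfaction score

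*Protocol article*

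**What the plan says.** The Statistical analyses section of the protocol article sets a repeated measures ANOVA with four measurements within subjects and intervention versus control between subjects. It then states that "intervention satisfaction, level of intellectual disability, age, baseline mindset, and gender will be tested as moderators of the effects" of the intervention, and gives the method: "These moderator effects will be tested using three-way interactions in our repeated measures design".

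The Background attaches a directional hypothesis to three of these moderators, satisfaction among them: "We hypothesize that adolescents with higher intervention satisfaction scores, borderline intellectual functioning, and a fixed mindset at baseline will show larger increases in growth mindset".

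The section on intervention satisfaction says who supplies the data: "Participants in the intervention group will grade their satisfaction after each session of" the programme. For the overall Session Rating Scale score, "the average will be taken of the session satisfaction scores of the six sessions". Table 1 (Instruments/measures) marks satisfaction only in the column for sessions 1–6, with no entry at T0, T1, T2 or T3.

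The Procedure section says of the other arm: "Youth in the control group will receive care as usual". Controls are offered the programme only once the trial has ended.

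On a related point, the Statistical analyses section adds to the intention-to-treat analysis: "In addition, a completers only analysis will be conducted (i.e., participants that completed five or six sessions".

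**The concern.** A three-way interaction asks whether the difference between arms in change over time varies with the moderator. That needs moderator values in both arms. Satisfaction with the sessions exists in one arm only, so the article assigns to this variable a test that cannot be run. This is a conflict between a stated variable and a stated method, not a detail held over for an analysis plan. A later plan could resolve it only by overruling this text.

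The risk lies in what replaces the test. The analyst will have to improvise, and the natural substitute is a within-arm association between satisfaction and change, reported under the heading of moderation. Satisfaction is recorded during treatment. Adolescents who are already gaining may rate the sessions higher, and those with a better outlook may do so whatever the programme achieves. Such an association cannot show for whom the intervention works, which is the trial's secondary aim.

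**Working it through.** **Plan's own figures.** The article gives no figure for the moderator tests. Its sample size can be reproduced, and this shows that it does not depend on the point. Inputs from the Participants section: d = 0.25, two-sided alpha 0.05, power 0.80, three measurements. The within-person correlation is not given; I assume 0.5. With f = d/2 = 0.125, the noncentrality for group × time is f² × N × m/(1 − ρ) = 0.015625 × 106 × 3/0.5 = 9.94, on 2 and 208 df. Power is 0.807, and 106 is the smallest total with equal arms. Then 106/0.9 = 117.8, so 118, which 120 covers. Satisfaction enters nowhere.

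**Which terms the stated model needs.** With four time points (three time contrasts) and one continuous moderator:

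| Term | Columns |
|---|---|
| Intercept | 1 |
| Time | 3 |
| Group | 1 |
| Group × time | 3 |
| Moderator | 1 |
| Moderator × time | 3 |
| Group × moderator | 1 |
| Group × moderator × time | 3 |
| Total | 16 |

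**What can be estimated.** The rank of this design matrix was computed for 60 per arm. The degrees of freedom of the three-way term are the rank with it minus the rank without it.

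| Moderator in controls | Rank with term | Rank without | df of three-way term |
|---|---|---|---|
| Missing (satisfaction as planned) | 8 | 8 | 0 |
| Set to 0 | 12 | 12 | 0 |
| Set to 8 | 12 | 12 | 0 |
| Measured in both arms | 16 | 13 | 3 |

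The algebra agrees. Let g be 1 for intervention and 0 for control, and s the satisfaction score. If satisfaction is missing in controls, they drop out, g is constant, and every group term duplicates another column. If controls are given a constant c, then g·s = s − c + c·g, so the product is a linear combination of columns already in the model. The same holds after multiplying by each time contrast.

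The result is the same for either satisfaction score in the article, the mean session grade or the Session Rating Scale average, since both are built from session ratings.

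**Imputation.** The article imputes missing values at post-intervention and follow-up measurements. A control's satisfaction score is undefined rather than missing. Drawing values for controls would make the matrix full rank, but the estimate would come wholly from the imputation model.

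**What can be estimated instead.** Within the intervention arm (60 planned, 60 × 0.9 = 54 after the planned attrition), satisfaction × time is an ordinary two-way term with 3 df over four time points. If T0 mindset is a covariate and T1–T3 are the outcomes, the same 3 df split into 1 for satisfaction and 2 for satisfaction × time.

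**The case against.** The strongest reply is that little is at stake. Moderation is a secondary aim. Satisfaction is one of five moderators; level of disability, age, baseline mindset and gender exist in both arms and can be tested as written. The intention-to-treat comparison is untouched. All of this stands, and it limits the point to a correction of one secondary analysis.

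A reader might infer that the satisfaction hypothesis must be deleted. The documents do not require that. The Background contrasts adolescents with higher and lower satisfaction with the intervention, and that contrast lies within the intervention arm. What fails is the three-way test and the label of moderator.

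A reader might also infer that the completers analysis is biased in favour of the intervention by a substantial share of d = 0.25. The documents do not support this:

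- They do not say which controls enter that analysis, and they give neither a completion rate nor any link between attendance and outcome.
- Suppose completers are compared with all controls, the true effect is 0, and attendance has correlation r with outcome. The shift is r × φ(z)/p, where p is the completion share, z the matching normal cut-off and φ the normal density. For assumed p of 0.70 to 0.95 and r of 0 to 0.5, it runs from 0 to 0.248 SD, that is, from nothing to almost the whole planning effect. A negative r reverses the sign.
- A gap in level already present at T0 would cancel from group × time. Only a gap in change would matter.

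What remains is structural. No control can complete five or six sessions during the trial, so the comparison is not randomised. Adding such an analysis to intention to treat is common practice and not in itself an error.

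**Conclusion.** The point holds for the satisfaction moderator. As specified, time × group × satisfaction has 0 of the 3 degrees of freedom it needs. This follows from the article's own text and rests on no assumed figure. The Background hypothesis on satisfaction cannot be examined by the method the article assigns to it. It can be examined as an association among treated participants. The other four moderators, the primary analysis and the sample size are unaffected.

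The remark on completers is secondary: the analysis is non-randomised and supportive, and neither size nor direction of bias can be claimed from the documents.

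This should be corrected before analysis, but it does not threaten the trial's main conclusion.

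**What to change.** 1. In Statistical analyses, take satisfaction out of the list tested by three-way interaction and leave the other four as they are.
2. Add a separate sentence: *satisfaction and its interaction with time will be analysed within the intervention arm only, adjusted for mindset at T0, and reported as an exploratory association*. Name which satisfaction score is used.
3. Reword the satisfaction part of the Background hypothesis in the same terms, and note that satisfaction is measured after randomisation and may reflect benefit already gained.
4. Label the completers analysis as supportive and not a randomised comparison, and say which controls it includes.

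I would not replace the completers analysis by dividing the intention-to-treat difference by the share attending at least five sessions. That assumes no effect of attending one to four sessions, and the Intervention section places much of the core content there: brain plasticity, the two mindsets, goals, effort and strategies.

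The cost is a few sentences and one small analysis. The downside is that the satisfaction question no longer addresses moderation of the randomised effect and rests on one arm of 60.

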## Discussion

The present study protocol presents a randomized controlled trial testing the effectiveness of the online mindset intervention “The Growth Factory”. The intervention aims to develop a growth mindset in adolescents with intellectual disabilities. A growth mindset leads to higher levels of academic achievement and psychosocial development [16–18]. Therefore, we expect that adolescents in the intervention group will show larger improvements in their psychosocial development compared with adolescents in the control group. The primary aim of the present study will be to investigate whether “The Growth Factory” affects the following outcomes: mindset, empowerment, behavior problems, self-esteem, treatment motivation, therapeutic alliance, challenge seeking, and impact of social exclusion. The secondary aim will be to examine which factors moderate or mediate the effect of the online intervention “The Growth Factory”.

### Strengths and limitations

To our knowledge, this is the first full scale RCT study evaluating an online mindset intervention developed for adolescents with intellectual disabilities. RCT studies are considered the gold standard for evaluating efficacy in clinical research [69]. In addition, in contrast to the most RCT studies, we will not only focus on the effectiveness of the program, but also on the moderating and mediating factors of change (i.e., for whom and how the intervention works). Furthermore, the intervention is based on previous effective mindset interventions [20, 52] and the core principles of these interventions will remain intact in “The Growth Factory”. Moreover, the intervention is specifically adapted for adolescents with intellectual disabilities using the guidelines for effective interventions for people with intellectual disabilities [53]. An additional strength of the study is that the intervention paradigm has been pre-tested in a pilot study to improve the intervention for the target group and to ensure that it fits the information processing needs of these youth with special learning needs. Another strength of this study is that different locations of the residential care institute will participate in this study, as will different schools for special education across the country. For this reason, the participants in the current study will represent the diverse population of youth with intellectual disabilities. Furthermore, the triangulation of different data sources (self- and teacher reports, behavioral tasks at the last follow-up) across four measurement moments (pre-test, post-test and a 3 and 6 months follow-up) is a strength.

However, this study also has some limitations. The first is the lack of an additional program specifically developed for mentors and parents as the environment plays a crucial role in facilitating or inhibiting the development of a growth mindset [70, 71]. To diminish this limitation parents were provided with personal login codes to be able to participate in the intervention “The Growth Factory”. However, mentors were not provided with a login code to prevent intervention contamination to the control group, because it could be possible that youth from the intervention and control group were in their class or group. Another limitation is that we will not be able to include a third condition that acts like an active control group to ensure the effects can be uniquely ascribed to the intervention “The Growth Factory”. However, previous research showed that a mindset intervention was more effective than both a passive (no intervention) as well as an active control group [40]. An additional limitation is that the present study, in contrast to many previous studies on mindset interventions, does not measure the impact of “The Growth Factory” on academic achievement. The reason for this is that standardized testing is exceedingly complex in this context—it is not always the standard in special education and varies widely across special education schools. Finally, only short- and medium-term effects (3 and 6 months follow-up) will be investigated. In this way, no conclusions can be drawn about the longer-term effects of “The Growth Factory” on the psychosocial development of youth with intellectual disabilities.

### Implications for practice

If “The Growth Factory” proves to be effective, a significant contribution to the evidence-based treatment of empowerment in adolescents with intellectual disabilities will be provided. When adolescents with intellectual disabilities believe in the malleability of their capabilities and therefore experience more control over their own lives, this will subsequently help to improve their psychosocial outcomes. Furthermore, due to the online approach, dissemination and implementation of the intervention will be efficient and cost-effective and therefore the intervention “The Growth Factory” will be able to be used on large scale in residential care institutes and at special schools.

## Conclusion

Adolescents with intellectual disabilities are more likely to endorse a fixed mindset compared to their non-disabled peers. Mindset interventions can have positive impact on the academic achievements and psychosocial development of adolescents. This paper describes the design of an effectiveness study of the online intervention “The Growth Factory” developed to empower adolescents with intellectual disabilities by teaching a growth mindset. In addition, with this study we will also contribute to a further understanding of possible moderating and mediating effects of mindset interventions. By doing so we gain more insight into what works for whom and how it works when it comes to interventions aiming to develop a growth mindset. Furthermore, this is the first study evaluating an online mindset intervention specifically adapted to adolescents with intellectual disabilities. If “The Growth Factory” turns out to be effective, a significant contribution will be made to the evidence-based treatment empowering adolescents with intellectual disabilities.

